For this reason, we will conduct an interviewer-blinded, multi-centre randomised controlled trial with four parallel groups. The primary aim of which is to determine the effectiveness of the cognitive rehabilitation programme GRADIOR and the psychosocial stimulation platform ehcoBUTLER, separately or in a combined treatment, on the cognition, quality of life, activities of daily living, relationships with carers and depressive symptoms of people with MCI and PwD. Based on previous research, we hypothesise that people with MCI and PwD in the cognitive rehabilitation group using GRADIOR or combined treatment will improve their cognition in comparison to other treatment groups and/or the treatment as usual (TAU) group. A secondary aim is to examine the interaction between psychosocial stimulation and cognitive rehabilitation in order to discover their synergies or usefulness. The duration of the RCT is 1 year of treatment followed by a 1-year follow-up study.

A preliminary study on the usability of GRADIOR and ehcoBUTLER will be conducted through focus groups and users’ testing in order to identify any issues in the programme’s features which may potentially influence its effectiveness in MCI and PwD. Additional data will be collected and any incidents will be monitored to improve the final usability of both programmes.

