### Sample size

Maximal sample size for the study was set at 400 participants with dementia and MCI. We considered a 15% dropout by participants during the 12 months of interventions and 12 months of follow-up. Therefore, the final sample size for the study is likely to be 340 participants.

Considering that the standard deviation of the selected population in the selected variables of the study was unknown and the population size was undetermined, we opted for a calculation of the sample size for an infinite population with the maximal level of variability of the dependent variables of the study (*p* = *q* = .5). If the population scattering parameters are unknown, this calculation allows for a more conservative sample size, meaning the biggest sample size [30].

The calculation was executed using the following equation (α = .05):$$ n=\frac{Z_{\raisebox{1ex}{$\propto $}\!\left/ \!\raisebox{-1ex}{$2$}\right.}^2\ast {0.5}^2}{e^2}, $$

where 0.52 is a maximal variability (*p* * (1 − *p*)), *Z*_∞/2_ corresponds to scores in the percentile *α*/2 (.025) of a normal distribution, and *e* corresponds to the error acquired for the desired sample size, with a result of *e* = 5.3% for a sample size of 340 participants.

On the other hand, based on the Friedman table for determining effect size [31], for the primary outcome measure ADASCog to achieve 80% power (alpha 0.05) on a sample of 340 participants we are looking for an approximate effect size of 0.30, which is similar to a separate study protocol on cognitive rehabilitation in PwD [9].

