### Outcome measures and hypotheses

#### Primary outcome measures

GRADIOR stimulates cognitive functioning, which is reflected in changes in separate cognitive domains. Outcome measures were selected accordingly. The primary aim of the study is to determine whether the cognitive rehabilitation programme GRADIOR improves cognition of people with MCI and PwD in a specific (GRA) or combined treatment group (COM). Based on previous research in this area, and our previous experience with the GRADIOR programme in a clinical setting, we expect that the two treatment groups using GRADIOR solely and in combination (COM) will achieve significantly higher scores in cognitive testing than the TAU group after 4 and 12 months of treatment. The primary outcome measure will be an ADASCog Cognitive Subscale [36].

The change in cognitive performance after a period of 4 months and 12 months in comparison with baseline results will be measured in all study groups using the *ADASCog Cognitive Subscale* [36] as the primary outcome, which evaluates cognitive performance in memory, praxis, orientation and language. Additionally, the Spanish version of the *Mini-Mental State Examination (MMSE)*, consisting of 35 questions [37], will be used*.* For a more comprehensive evaluation of a participant’s cognitive profile, we will use a variety of tests: the *Clock Drawing Test* [38] for general cognitive and spatial functioning, *WAIS III – Coding digit symbol, Calculus and Digit Span* subtests [39] to evaluate processing speed, numeric reasoning and working memory respectively, the *Rivermead pattern recognition test* [40] for visual memory, *Trail-making tests A and B* [41] to monitor motor functioning, executive functioning and visual-spatial abilities (part A) and also sustained attention (part B), the *Cambridge Cognitive Examination (CAMCog) – matrices* subtest [42] to examine intellectual ability, analogic reasoning and abstraction capacity and *Semantic and phonologic verbal fluency* [43] and [44] on animal category and letters P, M and R.

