### Analysis

Statistical analysis will be conducted using programme IBM SPSS v.23. A descriptive analysis of demographic and personal data will be conducted and results will be compared between all groups. Firstly, an analysis of normality and homogeneity of the data will be conducted. For normally distributed data, the repeated measures analysis of variance (ANOVA) will be used to examine the hypotheses in inter-subject and intra-subject analysis as well as in their interaction. This will be applied to all outcome measures in a comparative analysis of the data collected at from baseline, after 4 months and 12 months of the treatment. In case of non-homogeneous data, non-parametric methods will be used for analysis (Mann–Whitney *U* test, Kruskal-Wallis analysis of variance, Wilcoxon signed-rank test, calculation of Spearman’s correlation coefficient, etc.). Bonferroni/Dunnet corrections will be applied during post-hoc analysis if needed. The possible effects of randomisation bias will be analysed using linear-mixed models including within-group and between-group factors. The significance level will be set at *α* = .05.

Effect sizes and their respective standard errors (SE) and confidence intervals will be estimated as Standardised Mean Change Index (dMR) for within-group comparisons, and as Standardised Mean Index difference (dC) for between-group comparisons, and corrected for small sample sizes [54]:

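### The primary aim and hypothesis are worded more widely than ADASCog, the one primary outcome that the protocol names

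*Protocol article*

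**What the plan says.** **Outcome.** The section on primary outcome measures names one measure, "The primary outcome measure will be an ADASCog Cognitive Subscale [36", and its next paragraph again gives ADASCog "as the primary outcome, which evaluates cognitive performance in memory, praxis, orientation and language". The Sample size section states power "for the primary outcome measure ADASCog to achieve 80% power (alpha 0.05) on a sample of 340 participants".

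**Aim.** The last part of the Background gives the primary aim as effectiveness of both programmes, alone or combined, "on the cognition, quality of life, activities of daily living, relationships with carers and depressive symptoms of people with MCI and PwD". The only secondary aim there is the interaction between the two interventions. The section on primary outcome measures says instead: "The primary aim of the study is to determine whether the cognitive rehabilitation programme GRADIOR improves cognition". The section on secondary outcome measures then covers quality of life, depressive symptoms, activities of daily living and the carer relationship. It also assumes that participants with dementia who receive GRADIOR alone will not improve on them.

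**Hypothesis.** The two groups using GRADIOR "will achieve significantly higher scores in cognitive testing than the TAU group after 4 and 12 months of treatment".

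**Tests under the primary heading.** Besides ADASCog there are 11 scores: MMSE, Clock Drawing, three WAIS-III subtests, Rivermead pattern recognition, Trail-making A and B, CAMCog matrices, and semantic and phonologic fluency. None is called secondary or exploratory.

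**Analysis.** Repeated measures ANOVA is to examine the hypotheses. "This will be applied to all outcome measures in a comparative analysis" of baseline, 4-month and 12-month data. Alpha is .05, and Bonferroni or Dunnett corrections apply post hoc, if needed.

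**The concern.** A primary outcome limits what a trial may claim only if the aim and the hypothesis refer to it. Here they do not. Suppose that ADASCog shows no difference and one subtest does. An author could then say that the groups scored higher in cognitive testing and that the aim of improving cognition was supported. If depressive symptoms alone improved, the aim in the Background could be called partly met. The article does not say which statement governs.

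At stake is what the trial can report as its primary result, and whether the stated 5% level belongs to that result.

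**Working it through.** **1. The plan's own power figure.** For two groups of 170 (340 in all), two-sided .05 and 80% power, the detectable standardised difference is (1.960 + 0.842) × √(2/170) = 0.304. This agrees with the statement "we are looking for an approximate effect size of 0.30". It is a calculation for one outcome tested once at .05, so the power statement belongs to ADASCog and not to a battery. Whether it suits a comparison of two of the four arms is a separate question.

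**2. The statements side by side.**

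| Place | Scope |
|---|---|
| Sample size | ADASCog |
| Primary outcome measures, named outcome (twice) | ADASCog |
| Primary outcome measures, aim | cognition |
| Primary outcome measures, hypothesis | cognitive testing, no test named |
| Background, primary aim | five domains |
| Background, hypothesis | cognition |
| Secondary outcome measures | the four non-cognitive domains |
| Analysis | all outcome measures, .05 |

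The four non-cognitive domains are thus part of the primary aim in one place and secondary in another.

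**3. Number of scores.** ADASCog plus 11 others makes 12. Table 2 shows 10 cognitive rows because the two Trail-making parts share a row, as do the two fluency tests.

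**4. Conditional false-positive chance.** Assume no true effect, one arm against TAU at one visit, and that any one significant score is taken to meet the hypothesis. The documents give no correlations between tests, so an equal correlation ρ is assumed.

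- Independent scores: 1 − 0.95¹² = 0.46.
- Correlated scores: the probability that the largest of 12 equicorrelated standard normal statistics exceeds the critical value in absolute size, by simulation.

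| Critical value | ρ = 0.3 | ρ = 0.5 | ρ = 0.7 |
|---|---|---|---|
| 1.96 (no correction) | 0.40 | 0.32 | 0.23 |
| 2.35 (Dunnett, three arms against TAU) | 0.18 | 0.14 | 0.10 |

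Counting 10 scores instead of 12 gives 0.35, 0.29 and 0.21 without correction, so the result does not depend on how the paired tests are counted.

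**5. What remains with ADASCog alone.** Two GRADIOR arms against TAU at two visits are four tests. Without correction, the chance of at least one false positive is 1 − 0.95⁴ = 0.185 if they are independent. It is about 0.155 with assumed correlations of 0.5 between arms and 0.6 between visits. Closing the endpoint wording does not change this.

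**The case against.** The strongest reply is that the endpoint is already fixed. The sentence directly after the hypothesis names ADASCog, and so do the next paragraph and the power statement, each time in the singular. The other tests are introduced as additions that give a fuller cognitive profile. The hypothesis in the Background, right after the five-domain aim, is confined to cognition. The hypothesis under the primary outcome measures speaks of both groups and both visits, and nothing says that a single test is enough.

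Most of this stands. A reader might infer that the primary endpoint family is open and that a primary claim may rest on whichever measure turns out significant. The documents do not support that: such a claim would contradict the named outcome.

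A reader might also take 0.32 as the trial's error rate. It is not. It needs an any-one-test rule that the protocol does not state, and no correction. The Analysis section provides for a post-hoc correction, although only if needed. The correction lowers the figure but is not described as acting across outcomes.

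Detailed handling of supportive tests may also properly sit in an analysis plan that is not shown. That does not remove the conflict between the two statements of the primary aim, or the hypothesis that leaves out the named outcome. Both are in the article's own text.

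**Conclusion.** The point holds as a mismatch of wording: one primary outcome is named, and the aim and hypothesis are wider than it. The contradiction over the primary aim is plain and rests on no assumption.

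The size is conditional. If one significant score out of 12 were accepted, the false-positive chance would be roughly two to eight times .05 (0.10 to 0.40), depending on the threshold and on the assumed correlations of 0.3 to 0.7. For a test restricted to ADASCog these figures do not apply.

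The change is worth making because it settles what may be claimed as the primary result.

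**What to change.** 1. In the section on primary outcome measures, state the hypothesis for ADASCog only.
2. In the Background, align the primary aim with that section, and make quality of life, activities of daily living, the carer relationship and depressive symptoms secondary aims.
3. Move the other 11 cognitive scores under the secondary outcome measures. Either label them exploratory, or test them with a Holm correction only after ADASCog is significant.

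This needs wording only and no new data. The cost is that the primary aim can no longer be claimed from a subtest or a non-cognitive domain. The handling of the two GRADIOR arms and the two visits on ADASCog still has to be settled separately.

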#### Secondary outcome measures

Changes in quality of life (QoL) scores will be measured using the *EuroQol EQ5D-5 L* [45] which assesses quality of life from five dimensions, and the *Luben Social Network Scale (LSNS)* [46] which looks at social engagement, including relationships with family and friends. QoL scores will be compared between all the intervention groups and with the control group to determine which intervention obtains the best results and most influences the outcome. We will compare scores for each intervention group at 4 and 12 months in order to determine at which point in the treatment the various interventions most influenced quality of life. All participants will be assessed and compared using the *Geriatric Depression Scale (GDS)* [47], a 15-item version of a self-rating scale, in order to determine which type of intervention, if any, has an influence on depressive symptoms in PwD. Demographic data, activities of daily living (instrumental – IADL and non-instrumental – ADL), functional aspects and cost-effectiveness will be assessed using the *InterRAI Home Care* [48]. The quality of the relationship between the participants and their carers will be assessed using the *Quality of Carer-patient Relationship (QCPR) questionnaire* [49].

As GRADIOR focuses solely on cognitive rehabilitation, we assume that those participants with dementia receiving only the GRADIOR treatment will not see improvements in their quality of life, depressive symptoms, the quality of their relationships with a carer and/or activities of daily living after 4 or 12 months.

At the beginning of the study, participants will also receive the *Everyday Technology Use Questionnaire (ETUQ)* [50]. This will assess their perceptions about technology, difficulties encountered when using technology, and their degree of experience with technology that might be relevant for the study.

Carers will also be assessed at the same time as participants, whereby we will evaluate the following: their anxiety using the *State-Trait Anxiety Inventory (STAI)* [51], symptoms of depression with the *Beck Depression Inventory II (BDI-II)* [52], carer overload using the *Caregiver Burden Interview – Zarit Test* [53] and the quality of their relationships using the *Quality of Carer-patient Relationship (QCPR*) *questionnaire* [49]. We anticipate that GRADIOR will positively influence carer-outcome measures, and therefore, we hypothesise that in both intervention groups using GRADIOR, caregiver burden, anxiety and depression will decrease, and the relationship between the carer and the PwD will improve.

The data collected from the InterRAI Home Care Assessment will be used to analyse the cost-effectiveness of the treatment and its impact on health. The economic evaluation will employ a cost-consequences framework evaluating the associated costs and outcomes of the three types of interventions, in comparison to usual care. The evaluation will also assess the main sources of costs associated with the interventions. Primary analysis will be based on the most plausible real-world costs, including the cost of the technology and technical progress. The support costs for GRADIOR and ehcoBUTLER associated with technical aspects of installation, maintenance of hardware and information, as well as communication technology input related to software and data management, will be based on data gathered from sites. This will also include the input of professionals for guiding participants and support provided to participants throughout the intervention. For a complete list of the assessment tests used and the time schedule see Tables 2 and 3 respectively.

**Table 2 Tab2:** Assessments

Activity/assessment	Staff member	Time	Pre-study	Pre-study baseline	2	4	6	8	10	12	16	24
Usability study	Interviewer	N/A	X									
Focus group		90										
SUS		N/A										
Consent Form	Study coordinator	5	X	X		X				X	X	X
Inclusion/exclusion criteria	Study coordinator	N/A	X									
DSM-5 criteria	Interviewer	N/A	X									
Cognitive assessment	Interviewer	106										
MMSE		20		X		X				X	X	X
ADASCog		40		X		X				X	X	X
WAIS III: Calculus		5		X		X				X	X	X
WAIS III: Digit Span		5		X		X				X	X	X
WAIS III: Coding digit symbol		2		X		X				X	X	X
TMT A and B		10		X		X				X	X	X
Semantic and phonologic verbal fluency		4		X		X				X	X	X
CAMCog matrices		5		X		X				X	X	X
Clock Drawing Test		10		X		X				X	X	X
Pattern recognition test		5		X		X				X	X	X
ADL/iADL (InterRAI HC)	Interviewer	N/A		X		X				X	X	X
Quality of life	Interviewer	20										
EQ5D-5 L		5		X		X				X	X	X
LSNS (Luben)		15		X		X				X	X	X
Mood	Interviewer	15										
GDS		15		X		X				X	X	X
Patient-carer relationship		N/A										
QCPR				X		X				X	X	X
Technological assessment	Interviewer	N/A										
ETUQ				X								
Randomisation	Study coordinator	N/A		X								
Treatment (group-specific)	Study coordinator	N/A			X	X	X	X	X	X		
Termination Form	Study coordinator	N/A	As needed throughout the study									
Adverse Event Form	Study coordinator	N/A	As needed throughout the study									
Progress notes	All	N/A	X	X		X				X		
Communication log	All	N/A	Every phone or in-person contact outside of regular visit									

*ADASCog* Alzheimer’s Disease Assessment Scale – Cognitive Subscale, *ADL* activities of daily living, *CAMCog* Cambridge Cognition Examination, *EQ5d-5 L* EuroQoL 5 dimensions, 5 levels, *ETUQ* Everyday Technology Use Questionnaire, *GDS* Geriatric Depression Scale, *LSNS* Luben Social Network Scale, *MMSE* Mini Mental State Examination, *N*/*A* not applicable, *QCPR* Quality of Patient-carer Relationship, *SUS* System Usability Scale, *TMT* Trail-making test

**Table 3 Tab3:** Time schedule

Activity/month	Responsible	−3	−2	−1	0	1	2	3	4	5	6	7	8	9	10	11	12	13	14	15	16	17	18	19	20	21	22	23	24	25	26	27
Project development	Primary researchers	X	X	X																												
Ethical Committee approval	Primary researchers			X																												
Protocol preparation	Primary researchers	X	X	X																												
Usability study (US)		X	X	X	X	X	X	X	X	X	X	X	X	X	X	X	X	X														
Informed consent for US	Researchers responsible for US			X																												
Participants selection for US	Researchers responsible for US			X																												
*Focus group*	Researchers responsible for US			X																												
Users’ testing	Researchers responsible for US			X																												
Intermediate evaluation	Researchers responsible for US				X	X	X	X	X	X	X	X	X	X	X	X	X															
Incidence registration	Researchers responsible for US																	X														
Randomised controlled trial		X	X	X	X	X	X	X	X	X	X	X	X	X	X	X	X	X	X	X	X	X	X	X	X	X	X	X	X			
Interviewers’ training	Responsible for interviewers		X	X																												
Participants selection	Responsible for interviewers			X																												
Baseline evaluation	USAL			X																												
Treatment revision	Interviewers			X					X																							
Participants evaluation	Interviewers								X								X				X								X			
Randomisation	USAL/Sacyl/INTRAS			X																												
Intervention implementation	Primary researchers				X	X	X	X	X	X	X	X	X	X	X	X	X	X	X	X	X	X	X	X	X	X	X	X	X			
Data management and results		X	X	X	X	X	X	X	X	X	X	X	X	X	X	X	X	X	X	X	X	X	X	X	X	X	X	X	X	X	X	X
Database development	IBIP + USAL			X	X																											
Data collection	Interviewers				X				X								X				X								X			
Data analysis	Primary researchers + USAL														X	X	X	X	X	X	X	X	X	X	X	X	X	X	X	X	X	X
Data coding and upload	Primary researchers + USAL			X	X				X								X				X								X			
Hypotheses testing	Primary researchers + USAL								X	X	X	X	X	X	X	X	X	X	X	X	X	X	X	X	X	X	X	X	X	X	X	
Results and conclusions	Primary researchers				X	X	X	X	X	X	X	X	X	X	X	X	X	X	X	X	X	X	X	X	X	X	X	X	X	X	X	X
General project evaluation	Primary researchers	X	X	X	X	X	X	X	X	X	X	X	X	X	X	X	X	X	X	X	X	X	X	X	X	X	X	X	X	X	X	X
Dissemination		X	X	X	X	X	X	X	X	X	X	X	X	X	X	X	X	X	X	X	X	X	X	X	X	X	X	X	X	X	X	X
Dissemination of results (publications, conference presentations)	Primary researchers								X	X							X	X	X	X	X	X	X	X	X	X	X	X	X	X	X	X

*IBIP* Iberian Institute of Research in Psychosciences*, Sacyl* Health system in Castile and Leon, *USAL* University of Salamanca

### Analysis

Statistical analysis will be conducted using programme IBM SPSS v.23. A descriptive analysis of demographic and personal data will be conducted and results will be compared between all groups. Firstly, an analysis of normality and homogeneity of the data will be conducted. For normally distributed data, the repeated measures analysis of variance (ANOVA) will be used to examine the hypotheses in inter-subject and intra-subject analysis as well as in their interaction. This will be applied to all outcome measures in a comparative analysis of the data collected at from baseline, after 4 months and 12 months of the treatment. In case of non-homogeneous data, non-parametric methods will be used for analysis (Mann–Whitney *U* test, Kruskal-Wallis analysis of variance, Wilcoxon signed-rank test, calculation of Spearman’s correlation coefficient, etc.). Bonferroni/Dunnet corrections will be applied during post-hoc analysis if needed. The possible effects of randomisation bias will be analysed using linear-mixed models including within-group and between-group factors. The significance level will be set at *α* = .05.

Effect sizes and their respective standard errors (SE) and confidence intervals will be estimated as Standardised Mean Change Index (dMR) for within-group comparisons, and as Standardised Mean Index difference (dC) for between-group comparisons, and corrected for small sample sizes [54]:

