To ensure a high number of participants finish the study and participate in as many treatment and evaluation sessions as possible, they will be offered different dates of evaluation. The data collected from participants who prematurely finish the study will be used for partial data analysis. Interviewers involved in assessment and data collection will be trained centrally in trial requirements, ensuring that they have full knowledge of all measurement scales and know how to correctly administer tests. All interviewers will also receive training in the outcome measures used during the trial and will comply with the same administration criteria and standards for every scale and measurement used. Interviewers will have access to video guidelines for the correct administration and scoring of all tests used during the study. During training, interviewers will learn how to administer each test used in the study following the video guidelines. Subsequently, to ensure correct scoring, interviewers will have to score a tested person featured in the video with a requirement of inter-rater reliability of *κ* = 0.80 (between the interviewer in the training and the interviewer from the video). Study coordinators will be responsible for correct data collection and administration of all tests by interviewers.

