## Discussion

We will conduct a RCT with a long-term cognitive rehabilitation intervention and follow-up. This innovative RCT aims to determine the influence of a long-term, computerised, cognitive rehabilitation programme on people with MCI and PwD in comparison to psychosocial stimulation and TAU. The preliminary usability study will focus on ensuring that this type of treatment is more convenient and beneficial for older people, as well as for healthcare professionals.

Limitations of the study are related to the long duration of the treatment along with the 1 year follow-up. Therefore, we expect a large number of participants to drop out due to loss of interest, medical reasons or worsening of a related health condition, changes in life situation, etc. This potential dropout rate has been considered in the sample size calculation to ensure the success of the trial. We also foresee the potential for interviewers and staff to drop out during the study. In this case, every new member of staff recruited will be informed about the study and every new interviewer will undergo the same training in evaluation tools as those recruited at the start of the study.

For ethical and practical reasons, participants in this study will not be blinded to the intervention condition. Huntley et al. [55] recommend conducting single-blinded psychosocial intervention RCTs to minimise other factors, such as socialisation, when using the TAU control group (e.g. patient blinded and assessor blinded, but not therapist blinded). However, this is difficult to apply in practice due to ethical reasons. Therefore, we are conducting a single-blinded RCT with four parallel groups. In this study, all interviewers will be blinded to participants’ treatment allocation. Study coordinators who will manage and adjust the GRADIOR treatments of all participants will do so only based on data obtained from the programme and manage this under a participant’s code (Fig. 1 and Additional file 1).

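### The fixed hypothesis test, repeated-measures ANOVA in SPSS, in its classical form omits anyone with a missing visit and leaves early leavers to an undefined partial analysis, which costs precision and can bias the arm comparison in either direction

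*Protocol article*

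**What the plan says.** - **Software and method (Analysis).** "Statistical analysis will be conducted using programme IBM SPSS v.23". For normally distributed data, "the repeated measures analysis of variance (ANOVA) will be used to examine the hypotheses in inter-subject and intra-subject analysis"; the same sentence adds the interaction of the two. The outcomes and visits covered are fixed as well: "This will be applied to all outcome measures in a comparative analysis of the data collected at from baseline, after 4 months and 12 months". Non-parametric tests are the fallback, and Bonferroni or Dunnett corrections are available post hoc.
- **Mixed models (Analysis).** "The possible effects of randomisation bias will be analysed using linear-mixed models including within-group and between-group factors". No other use is given for them.
- **Early leavers (Treatment adherence).** "The data collected from participants who prematurely finish the study will be used for partial data analysis". The term is not explained.
- **Dropout (Sample size).** A 15% loss is allowed over the 24 months, so that "the final sample size for the study is likely to be 340 participants".
- **Dropout (Discussion).** "we expect a large number of participants to drop out". The reasons listed include loss of interest, medical reasons, a worsening health condition and changes in life situation.
- **Hypothesis (Primary outcome measures).** GRA and COM are each expected to do better than TAU in cognition at 4 and at 12 months. ADAS-Cog is the primary outcome, as change from baseline.

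**The concern.** Three choices in the text combine badly. The hypothesis test needs all three visits from each participant. The people who will lack a visit are sent to an analysis that nobody can identify in advance. The one method named that could keep their 4-month data, the linear mixed model, is reserved for another purpose.

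The missing data may well be informative. The protocol itself links some dropout to worsening health. Burden also differs by arm: GRA has three to four sessions a week, PSS at least 5 hours of platform use a week, COM a mixture of both, and TAU no study sessions. Participants know their allocation. If people who decline leave one arm more readily than another, a comparison of those who remain is no longer the randomised comparison.

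There is a second, separate issue. The inter-subject term compares arm means over three visits, one of which precedes treatment.

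**Working it through.** **1. The plan's own figure.** 400 × (1 − 0.15) = 340. This reproduces. If all 60 were lost by month 12, evenly by arm, 85 per arm would be complete. The 15% covers 24 months, so the 12-month loss could be smaller.

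**2. Precision.** For one pair of arms, two-sided α = 0.05, SD = 1, difference d = 0.30 (the value in Sample size, read here as a standardised difference): power = Φ(d / √(2/n) − 1.96), and the detectable d at 80% power = 2.80 × √(2/n).
- n = 85: √(2/85) = 0.153; power 50%; detectable d 0.43.
- n = 100: √(2/100) = 0.141; power 56%; detectable d 0.40. This is an upper bound, because leavers contribute only part of their data.

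**3. Bias from omitting leavers.** The protocol gives no visit correlations and no dropout by arm, so these are assumptions. Dropout after month 4 follows a logistic model in the standardised change from baseline to month 4.

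*No true effect, all visit correlations 0.7, slope 1.5; bias in 12-month change, favouring the active arm:*

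| Dropout, active v TAU | Completers | Likelihood-type estimate using 4-month data |
|---|---|---|
| 15% v 15% | 0.00 SD | 0.00 SD |
| 20% v 10% | 0.04 SD | below 0.004 SD |
| 25% v 5% | 0.08 SD (type I error about 10.6% at 100 per arm) | below 0.004 SD |

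With baseline adjustment, the completer bias in the two unequal rows is 0.03 and 0.06 SD (type I error 5.5% and 8.5%).

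*True 12-month difference −0.30 SD (negative favours treatment), correlations 0.80, 0.80 and 0.65, slope 1; completer estimate:*

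| Dropout | Completer estimate |
|---|---|
| Random, 15% in both arms | −0.30 |
| Decliners leave both arms equally, 15% | −0.30 |
| Decliners leave the active arm only, 15% in both | −0.37 |
| Decliners leave TAU only, 15% in both | −0.23 |
| Decliners, 20% v 10% | −0.34 |
| Decliners, 25% v 5% | −0.39 |

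The likelihood-type estimate is within 0.002 SD of the truth in every row. So bias needs dropout that is related to outcome and differs by arm in rate or in that relation, and it can go either way.

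**4. Limit of the remedy.** Repeat the first table's scenario, but let dropout depend on decline after month 4, which is not observed in leavers. The likelihood-type estimate then has bias 0.06 SD (20% v 10%) and 0.12 SD (25% v 5%). Completers have about 0.04 and 0.08 to 0.09 SD. The near-zero bias in step 3 holds because dropout there depended only on observed data.

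**5. Inter-subject term and interaction.** Assume 0.30 SD in GRA and COM at both post-baseline visits, none in PSS or TAU, correlation 0.7 and 85 per arm.
- The three-visit mean difference is (0 + 0.30 + 0.30)/3 = 0.20 SD, with variance (1 + 2 × 0.7)/3 = 0.80.
- Inter-subject F: λ = 85 × 4 × 0.10² / 0.80 = 4.25 on 3 and 336 df; power 38%.
- Group-by-time F: λ = 85 × 0.06 / 0.30 = 17.0 on 6 and 672 df; power 89%. Here 0.06 is the sum of squared interaction effects over the four arms and three visits.
- One pairwise contrast of three-visit means: SE = √(2 × 0.80/85) = 0.137; 0.20/0.137 = 1.46; power 31%.
- One baseline-adjusted 12-month contrast: SE = √(2 × 0.51/85) = 0.110, where 0.51 = 1 − 0.7²; 0.30/0.110 = 2.74; power 78%.

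Like for like, then, a single pairwise contrast has 31% power with baseline averaged in and 78% with baseline as covariate, both unadjusted for multiplicity.

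**The case against.** **A reader might infer that the plan commits to a completer analysis. It does not say so.** The 340 is a dropout allowance in a sample-size section, not an analysis set. The sentence on early leavers says that their data will be used, not that they are excluded. Analysis sets are often left to an analysis plan that is not shown. This stands as far as it goes: the restriction follows from the named method, not from any sentence. But the method itself is stated, and a later plan could keep leavers in the main test only by departing from it.

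**A reader might infer that the treatment effect is diluted. That holds for the inter-subject term only.** The group-by-time interaction is also planned, corresponds to change from baseline, and is well powered in step 5. Post-hoc corrections and between-group effect sizes with confidence intervals go some way towards arm-level answers. What remains is that the interaction F alone identifies no arm or visit, while the hypothesis concerns GRA v TAU and COM v TAU.

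**A reader might infer that the comparison is biased. That is conditional.** The 15% is not split by arm, several listed reasons for leaving have no evident link to cognition, and equal dropout with an equal relation to outcome gives no bias. TAU participants may also join other programmes on their own initiative, so TAU should not be described as receiving nothing. The 25% v 5% split is an extreme case.

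**The mixed model is no cure-all**, as step 4 shows, and the non-parametric fallback need not omit the same people. Both points stand. The fallback still does not secure an analysis of all participants as allocated.

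**Conclusion.** The concern holds in a limited form. The protocol fixes a test that in its classical form omits participants with a missing visit, leaves the handling of leavers undefined, and gives the more suitable method a different job.

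If the full 15% is lost by month 12, the detectable pairwise difference is 0.43 SD instead of 0.40 SD at best. The possible bias is about 0.04 SD at 20% v 10% outcome-related dropout and 0.08 SD at 25% v 5%. The latter is 0.08/0.30, about a quarter of the effect the trial looks for. Bias is nil if dropout has the same rate and relation to outcome in all arms, and the direction cannot be predicted. These bias figures rest on assumed correlations, dropout splits and dropout mechanisms.

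The dilution concerns the inter-subject term alone. Because it affects the primary comparison and is easily changed, it should be settled before analysis begins.

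**What to change.** 1. Make the linear mixed model the primary analysis of ADAS-Cog. Include all randomised participants as allocated and all available post-baseline visits, with arm × visit and baseline ADAS-Cog as covariate.
2. Report the GRA-TAU and COM-TAU contrasts at both 4 and 12 months, with the multiplicity correction already planned. This keeps the stated 4-month hypothesis.
3. Replace the sentence on partial analysis of early leavers with a statement that all their available visits are used.
4. Keep the completer repeated-measures ANOVA as a sensitivity analysis.
5. Add a sensitivity analysis for dropout that depends on unobserved decline, because the mixed model removes bias only when dropout depends on observed data.

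The cost is rewording in the Analysis and Treatment adherence sections and slightly more analysis work. The model is already named in the plan, and no extra data are needed.
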